# Towards seeing the visual impairments in Parkinson’s disease: protocol for a multicentre observational, cross-sectional study

**DOI:** 10.1186/s12883-019-1365-8

**Published:** 2019-06-25

**Keywords:** Parkinson’s disease, Ophthalmology, Eye, Visual impairment, Non-motor symptoms, Screening questionnaire, Survey

## Abstract

**Background:**

Visual disorders are common in Parkinson’s disease (PD) but their exact frequency and severity are unknown. Good visual functioning is crucial for patients with PD, because of their need to compensate for loss of automated motor control and their postural instability, forcing patients to guide their movements visually. Here, we describe the study design of a cross-sectional, multi-centre study aiming to: (1) validate the Visual Impairment screening questionnaire (VIPD-Q, which aims to identify PD patients who should be referred to an ophthalmologist for further assessment); (2) study the prevalence of visual disorders in PD; (3) study the severity and clinical impact of different types of visual disorders in PD; and (4) explore treatment options for ophthalmologic disorders in PD, as a basis for future guideline development.

**Methods:**

This study consists of two phases. In phase one, 750 PD patients and 250 healthy controls will be recruited to complete the VIPD-Q. In phase two, a subgroup of responders (*n* = 100) (with the highest and lowest scores on the VIPD-Q) will be invited for an extensive neurological and ophthalmological assessment. The in-depth ophthalmologic examination will serve as the “gold standard” for validating the VIPD-Q. Moreover, these assessments will be used to study associations between visual disorders and clinical presentation, in order to gain more insight in their clinical impact.

**Discussion:**

Our study will heighten the awareness of visual problems in PD and offers a robust starting point to systematically approach this subject. In current daily practice, the association between visual problems and PD is far from obvious to both patients and clinicians. Consequently, patients may not adequately report visual problems themselves, while clinicians miss potentially treatable visual disorders. Routinely asking patients to complete a simple screening questionnaire could be an easy solution leading to timely identification of visual problems, tailored treatment, restored mobility, greater independence and improved quality of life.

**Trial registration:**

Dutch Trial Registration, NL7421, Registered on 4 December 2018 – Retrospectively registered.

**Electronic supplementary material:**

The online version of this article (10.1186/s12883-019-1365-8) contains supplementary material, which is available to authorized users.

## Background

Parkinson’s disease (PD) is the second most common neurodegenerative disease in the developed world. The disease is characterized by a broad range of motor and non-motor symptoms [1]. Non-motor-symptoms include widely recognised examples such as gastrointestinal complaints, cognitive decline or autonomic dysfunction, but also less well appreciated ones such as visual impairment [2]. Visual problems can range from blurred vision, diplopia, reduced colour and contrast vision to visual field deficits, and sore, red, or fatigued eyes. Visual disorders in PD can be caused by different pathological mechanisms like retinal dopamine depletion or decreased dopaminergic innervation of the visual cortex [3, 4].

Almost 80% of visual impairments are treatable or preventable. But to achieve this, timely recognition is obviously pivotal [5]. However, in the field of PD, the presence of visual problems and the resultant visual impairment has remained severely under-recognized, both in research and in clinical practice. This is surprising, since the impact of visual problems is particularly vexing for patients with PD, because of their need to compensate for loss of automated motor control and their postural instability, forcing patients to guide their movements externally (and this include visual guidance) [6]. For example, visual cues such as stripes on the floor are commonly used in clinical practice to overcome freezing of gait [2, 7, 8]. Not being able to see these visual cues adequately may have an immediate impact on functioning in daily life. Indeed, visual disorders combined with postural instability and gait disability can increase the risk of falls and fall-related injuries such as hip fractures and head injuries [9, 10]. Other obvious consequences of visual deficits in PD include problems with driving and reading. Taken together, disorders of vision can lead to reduced physical activity, greater dependence, disability, injuries and reduced quality of life [11–13]. Yet, the exact frequency, type and severity of visual problems are unknown. The few prior studies on this subject showed inconclusive results, in part due to small samples or lack of a complete ophthalmologic examination [14–16]. Since many of these disorders can be treated effectively, educating patients and doctors about them can help to improve quality of life of patients with PD.

The current multicentre observational, cross-sectional VIP study: “Visual Impairment in Parkinson’s disease” is designed to promote knowledge about and recognition of symptoms, signs and causes of disturbed vision in people with PD. Our specific goals are to: (1) validate a screening questionnaire that aims to identify PD patients who should be referred to an ophthalmologist for further assessment; (2) determine the prevalence and severity of visual problems in PD; (3) study the impact of ophthalmologic disorders on clinical functioning (in particular on gait and balance control); and (4) explore treatment options for ophthalmologic disorders in PD, as a basis for future guideline development.

## Methods/design

Here we present our two-phase study, shown in Fig. 1. In phase 1, we aim to have the Visual impairment in Parkinson’s Disease Questionnaire (VIPD-Q) completed by at least 750 PD patients and 250 healthy controls. In phase 2, a subgroup of responders (*n* = 100) will be invited for an extensive neurological and ophthalmological assessment. The study is performed at three study sites (Radboud University Nijmegen Medical Centre, the Netherlands; the Medical University Innsbruck, Austria; and The OLVG hospital Amsterdam, the Netherlands). Each centre obtained local ethical approval (NL58535.091.16;AN2016–0181).The study will be performed in accordance with the Declaration of Helsinki. All participants have to give written informed consent prior to participation. This study is registered in The Dutch trial register: NTR 7663.

**Fig. 1 Fig1:**
[figure not shown]
Flowchart of the study design. Here we present our two-phase study. In phase 1, at least 750 PD patients and 250 healthy controls will complete the Visual impairment in Parkinson’s Disease Questionnaire (VIPD-Q). In phase 2, a subgroup of responders (*n* = 100) will be invited for an extensive neurological and ophthalmological assessment

### Phase 1: screening questionnaire

The VIPD-Q was developed by neurologists and ophthalmologists to detect a broad range of ophthalmologic disorders in PD patients. It is based on an extensive literature study, previous questionnaires, and common and disabling visual disorders in both PD patients and healthy older people [2, 11, 13, 15, 17–34]. The questionnaire includes 22 questions on visual problems, plus a standard set of demographic data (Additional file 1: Appendix 1). Answers are given on a 4-point Likert scale ranging from “never have problems” to “daily problems”, without possibility to give a neutral answer. As a second step, we grouped the questions according to the anatomical location of a visual disorder. These domains were agreed upon by a consensus procedure involving three independent ophthalmologists (one from each study site). They were asked to categorize the questions in four domains (Table 1: ocular surface, oculomotor, intra-ocular and optic nerve). Consensus was reached during a meeting with the three ophthalmologists. Six questions could not be categorized in one domain, but rather indicate the involvement of more than one anatomical domain. The VIPD-Q is designed as a patient self-scoring instrument and takes about 20 min to complete.

**Table 1 Tab1:** Domains and corresponding questions with possible diagnosis

Domains	Issues	Possible diagnosis	Question
Ocular surface	lacrimal fluid, eyelids, conjunctiva, cornea	dry eye disease, blepharitis, blepharospasm, conjunctivitis, low eye blink rate,	1: I have blurry vision, when I read or work on a computer. 2: I have a burning sensation or gritty feeling in my eyes. 3: I have mucus/slime or particles in my eyes or eyelids. 4: I have watery eyes.
Intra-ocular	lens, uvea, macula, retina	diabetic retinopathy, macular degeneration, retinal detachment, hypertensive retinopathy, micro-vascular retinopathy, cataract, refraction errors, glaucoma	5: When I read, some letters disappear. 6: Lines that should be straight, appear to be wavy or blurred. 7: I won’t go out alone in the evening or at night because my night vision is insufficient. 8: When I drive at night, the oncoming headlights cause more glare than before.
Oculomotor	eye movements, binocular cooperation	strabismus, convergence insufficiency, 3rd, 4th and 6th nerve palsies, nystagmus, gaze abnormality	9: Quick movements are hard to follow with my eyes. 10: I have double vision. 11: I can read better with one eye closed. 12: I have trouble with depth perception. I find it hard to say which one of two objects is closer.
Optic nerve	optic nerve disease	opticopathy, glaucoma (Mimics: structural lesion, hemianopsia)	13: Colours seem to be paler than before. 14: I can’t read plain text on a coloured or grey background. 15: I run into objects or people or feel that parts of my visual field are missing. 16. I have problems with rapid changes of light intensity. (For example, driving through a tunnel).

The Visual Impairment in Parkinson’s Questionnaire (VIPD-Q) has been divided in 4 domains as shown above. These domains were agreed upon by a consensus procedure involving three independent ophthalmologists (one from each study site). Six questions of the questionnaire could not be categorized in one domain, but rather indicate the involvement of more than one anatomical domain

The VIPD-Q is both available on paper and online (in English, German and Dutch). We will distribute the questionnaire using different strategies: (1) PD patients visiting the neurologic outpatient clinics at the three study sites (complete the questionnaire on site); (2) PD patients receiving care in one of the participating centres (will receive the questionnaire via post); and (3) PD patients interested in research, having registered on a platform for research and innovation in PD: www.parkinsonnext.nl (will receive the online questionnaire through e-mail). Healthy controls will be recruited by asking partners and family members of participating patients to also complete the questionnaire.

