
### Statistical analysis plan

95% Confidence intervals, means, standard deviations and frequency distributions will be calculated for all outcomes. Nonparametric variables (age, disease duration, LED, total score VIPD-Q) will be expressed as the median, interquartile range (IQR), minimum, and maximum. To compare groups, we will use the student’s t-test for parametric continuous variables and the Mann-Whitney U test for non-parametric continuous variables. All analyses will be performed with SPSS 22.0 (SPSS Inc., IBM, Chicago, IL, USA).

To address the first study objective (validity of the screening questionnaire), we will compare the results of the VIPD-Q with the ophthalmological assessments using analysis of intraclass correlation coefficient (ICC), with Cohen’s kappa. The results of the ophthalmological assessments will be categorized in visual disorders within the domains of the VIPD-Q (ocular surface, intra- ocular, oculomotor and optic nerve). We hypothesize moderate to good correlation (ICC > 0.5) between the scores on the domains based on the ophthalmological tests and the scores on the domains based on the screening questionnaire. We will also address correlation for the total score. In addition, we will calculate optimal cut-off points of the domains and total score of the VIPD-Q using the receiver operating characteristic (ROC).

For the second and third objective (determine the prevalence and severity of visual problems in PD; impact on clinical functioning), PD patients will be compared with healthy controls using chi-square-tests for categorical values (sex, education, co morbidity, visited ophthalmologist, visual aid, vision changes during the day, difficulties with daily activities, impact on quality of life) or Mann-Whitney U test for non-parametric continuous variables (age, total score VIPD-Q, score per domain). Furthermore, the relationship between falling, disease duration, MDS-UPDRS, hand-eye dexterity, gait and balance tests, and visual problems will be assessed using multiple linear regression analysis.

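### VIPD-Q item 15 mixes collisions with visual-field loss, so a PD–control difference in the optic-nerve domain score can be motor rather than visual

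*Protocol article*

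**What the plan says.** The Protocol article, section Phase 1: screening questionnaire, states: "The questionnaire includes 22 questions on visual problems". Answers are on a four-point frequency scale. Table 1 assigns sixteen of the items to four anatomical domains, four to each, by consensus of three ophthalmologists. Item 15, "15: I run into objects or people or feel that parts of my visual field are missing", is in the optic-nerve domain with items 13, 14 and 16. The possible diagnoses listed for that domain are "opticopathy, glaucoma (Mimics: structural lesion, hemianopsia"; no motor mimic appears.

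The Abstract gives the phase 1 sizes: "750 PD patients and 250 healthy controls will be recruited to complete the VIPD-Q". For the second and third objectives, the section Statistical analysis plan compares PD patients with controls by "Mann-Whitney U test for non-parametric continuous variables (age, total score VIPD-Q, score per domain". The same paragraph plans a multiple linear regression relating falling, disease duration, MDS-UPDRS, dexterity, gait and balance to visual problems. It does not say whether these are VIPD-Q scores or examination findings.

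On the motor side, the Background section says that "visual disorders combined with postural instability and gait disability can increase the risk of falls".

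**The concern.** Item 15 is double-barrelled. A respondent who bumps into things because of poor balance or gait, with an intact visual field, can truthfully report the problem, and the answer then counts as an optic-nerve symptom. Items elsewhere in Table 1 attribute the difficulty to sight: item 7 names night vision and item 9 refers to the eyes. The collision half of item 15 does not.

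The motor disorder is what separates the two groups being compared. A Mann-Whitney test takes no covariates. The motor measures (MDS-UPDRS, gait and balance tests) belong to phase 2, which examines patients only, and no eye examination of controls is described. Nothing in the PD–control comparison would therefore reveal that a shift in the optic-nerve score came from collisions. At stake is a published statement that PD patients have more optic-nerve symptoms than controls.

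**Working it through.** The article states no effect size, power or endorsement rate that bears on item 15, so there is no figure of the plan's to reproduce. The check is a sensitivity calculation.

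**Weight of the item.** With equal item weights (assumed), item 15 is 1/4 = 25% of the optic-nerve domain and 1/22 = 4.5% of the total.

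**Inputs from the article.** 22 items, a four-point scale, four optic-nerve items, 750 PD patients v 250 controls, Mann-Whitney test.

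**Assumed inputs.** Items scored 0–3; latent inter-item correlation 0.35; thresholds at the 55th, 80th and 93rd percentiles; identical true vision in both groups; two-sided 0.05. A share q of PD patients endorses item 15 for motor reasons only, at level 1, 2 or 3 with equal probability, and the item takes the higher of the visual and the motor answer.

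**Mean shift, by hand.**
- Mean item score without motor endorsement: 0.45 + 0.20 + 0.07 = 0.72.
- With motor endorsement: P(≥1) = 1; P(≥2) = 1 − 0.80 × 1/3 = 0.733; P(≥3) = 1 − 0.93 × 2/3 = 0.380. Mean 2.113.
- Gain per affected patient: 2.113 − 0.72 = 1.393 points. Group shift = 1.393 × q.

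**False significance by simulation (1,500 runs per row).**

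| q | PD patients affected (750 × q) | Mean shift (points) | Optic-nerve domain (0–12) | Total score (0–66) |
|---|---|---|---|---|
| 0 | 0 | 0 | 5.2% | 4.5% |
| 5% | 37.5 | 0.07 | 7.1% | 4.6% |
| 10% | 75 | 0.14 | 15.4% | 6.1% |
| 20% | 150 | 0.28 | 41.3% | 7.9% |
| 30% | 225 | 0.42 | 72.8% | 10.2% |

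The absolute shift is the same in both scores, but it is diluted in the 22-item total. Without item 15 the remaining three domain items have the same distribution in both groups by construction, so the error rate is nominal.

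**Cruder check.** The standard error of a 750 v 250 difference is √(1/750 + 1/250) = 0.073 SD. Suppose motor endorsement adds only one point in 20–30% of PD patients, and the domain SD is 2.2 (assumed). The shift is then 0.20/2.2 to 0.30/2.2 = 0.09 to 0.14 SD, or 1.2 to 1.9 standard errors. That is the same direction as the simulation, and smaller because the simulation adds 1.39 points per affected patient.

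**Regression, only if the VIPD-Q score is the visual measure.** With n = 100 and a motor effect of 0.5 or 1.0 latent SD on item 15 alone, the spurious correlation with motor severity is 0.15 or 0.27 for the optic-nerve score (significant in 32% or 79% of 3,000 runs). For the total it is 0.03 or 0.06 (6% or 9%). This is a two-variable correlation in a random sample. It models neither the covariates nor the selection of extreme scorers, so it shows the mechanism and is no estimate of the planned analysis's error rate.

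**The case against.** **The rate is assumed.** The article gives no frequency of motor-caused collisions. Its sentence on falls concerns visual disorders together with postural instability and says nothing of collisions from motor causes alone. At 5% endorsement the false-positive rate is close to nominal. Additional file 1, which holds the full questionnaire, is not shown, and its instructions may tell respondents to report only vision-related problems. All of this stands: the point is a risk with a range, and a bias has not been shown.

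**Validation might catch it.** Objective 1 sets each domain against the eye examination, which could expose a weak domain. But it does so in phase 2 patients only, so it cannot correct a comparison with unexamined controls.

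**This could be SAP detail.** A sensitivity analysis is often left to the SAP. The item wording, its domain and the comparison by domain score are, however, fixed in the article, and they create the risk.

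**Stronger readings that do not hold.** A reader might infer that the gait and falls analysis is contaminated as well. The documents do not support that as a fact. The Abstract says the phase 2 assessments will be used for associations with clinical presentation, and the third goal in the Background section concerns ophthalmologic disorders. Both point to examined findings, and in that case item 15 enters only through selection into phase 2. A reader might also extend the point to the total score, which barely moves, or to item 7 (not going out alone in the dark), which names insufficient night vision as the cause and does not share the defect.

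**Conclusion.** The concern holds for one result: the PD–control comparison of the optic-nerve domain score. That comparison can reach significance with equal vision in the two groups. The false-positive rate is about 7% if 5% of PD patients endorse item 15 for motor reasons, and about 73% if 30% do. These figures rest on the assumed endorsement share, equal item weights and the assumed item distribution. The total score is little affected, at about 5 to 10% over the same range. For the gait and falls regression there is only an ambiguity to close, because the visual measure is not named there and other text points to the examination. The optic-nerve score is one of four domain scores and has no stated primary status, so this affects the interpretation of a specific result and does not undermine the study's main answers.

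**What to change.** 1. Report the PD–control comparison of the optic-nerve domain with and without item 15. If the difference disappears without the item, do not attribute it to optic-nerve or visual problems.
2. In the objective 3 regression, state that visual problems means examined visual function from phase 2. If a VIPD-Q score is used instead, leave item 15 out of it.
3. Keep item 15 in the objective 1 validation, where its performance against the examination is itself of interest.

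Phase 1 recruitment is complete, so the item can no longer be split into two questions for these respondents. The cost is a second scoring of data already held and one clarifying sentence. The downside is that the score without item 15 loses the domain's only visual-field question and some true field loss with it. It therefore serves as a sensitivity analysis and should not replace the four-item score.

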### Phase 2: neurological and ophthalmological assessment

#### Patient collective and recruitment

From the responders of phase 1, a sample of 100 patients will be invited for a full clinical and ophthalmological assessment. Patients will be selected based on their scores on the VIPD-Q aiming to include 70 patients with and 30 patients without visual impairment, which is operationally defined as patients scoring the highest 30% or the lowest 30% on the screening questionnaire, respectively. Due to personnel capacity, a sample of 30 patients in the Netherlands (10 in the lowest 30% and 20 in the highest 30%) and 70 patients in Austria (20 in the lowest 30% and 50 in the highest 30%) will be selected and invited for the clinical and ophthalmological assessment. The OLVG hospital only participated in phase 1 of this study. Inclusion and exclusion criteria are described in Table 2. Selection will start after at least 250 questionnaires have been completed. (See Fig. 1).

**Table 2 Tab2:** Inclusion and exclusion criteria

Inclusion criteria	Exclusion criteria
Diagnosis of PD according to the UKPDSBB criteria	Hoehn and Yahr Parkinson’s staging score ≥ 4
The patient must be able and willing to give written informed consent	Secondary cause of parkinsonism as detected by history (e.g. drug-induced parkinsonism)
The patient must be willing to participate in all study related activities and visits	Secondary cause of parkinsonism as detected by investigation (e.g. vascular parkinsonism as detected by neuroimaging)
Age of onset Parkinson’s disease > 30 years	Dementia according to DSM-IV
Stable doses of Parkinson medications ≥4 weeks	Major depressive disorder according to DSM-IV
Current age ≥ 60 years	Psychotic disorder(s) according to DSM-IV
	Prior brain surgery (except deep brain stimulation)
	Previous eye surgery (except phacoemulsification for cataract and artificial lenses)
	Blindness in 1 eye
	Medication that influences normal visual function other than PD medication. (Detailed information, please see Additional file 2: Appendix 2)
	Systemic diseases that may cause eye problems (HIV, DM type I, type II if the patient had ophthalmologic therapy and/or abnormalities at last screening)
	Neurodegenerative diseases other than Parkinson’s disease
	History of lesions near the optic chiasm or occipital cortex
	Migraine

Inclusion and exclusion criteria of the Visual Impairment in Parkinson’s Disease study

Abbreviations: *UKPDSBB* United Kingdom Parkinson’s Disease Soeciety Brain Bank, *DSM-IV* Diagnostic and Statistical Manual of Mental Disorders IV, *HIV* human immunodeficiency virus, *DM type I* Diabetes Mellitus type I

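### Phase 2 examines only the highest and lowest 30% of VIPD-Q scorers, so its data cannot support an optimal ROC cut-off, or population accuracy figures, for the total score

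*Protocol article*

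**What the plan says.** The Background of the protocol article gives the questionnaire's purpose: to identify which PD patients should be referred to an ophthalmologist. The abstract makes the ophthalmological examination the reference standard.

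Under Patient collective and recruitment, "a sample of 100 patients will be invited for a full clinical and ophthalmological assessment". The selection rule follows: "Patients will be selected based on their scores on the VIPD-Q aiming to include 70 patients with and 30 patients without visual impairment". The article then explains how it tells these two groups apart: "which is operationally defined as patients scoring the highest 30% or the lowest 30% on the screening questionnaire, respectively". The abstract describes the same subgroup as those "with the highest and lowest scores on the VIPD-Q". Timing is given as: "Selection will start after at least 250 questionnaires have been completed".

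The Statistical analysis plan section compares domain scores with the examination, hypothesising an ICC above 0.5 for the domains, and adds a correlation for the total score without a threshold. It continues: "we will calculate optimal cut-off points of the domains and total score of the VIPD-Q using the receiver operating characteristic (ROC").

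Two further statements matter. Table 3 lists the screening questionnaire again among the phase 2 assessments, without saying which administration is analysed. Trial status expects phase 2 recruitment to be complete by May 2019; the article appeared on 25 June 2019.

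**The concern.** A ROC cut-off is chosen by comparing sensitivity and specificity at neighbouring score values. That needs examined patients on both sides of each candidate value. Here the middle 40% of scorers have no chance of being examined, and a referral threshold would be expected to fall among them.

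Selecting on the index test also changes the case mix. Clear high and clear low scorers are easier to tell apart than unselected patients, and high scorers are taken at 70 to 30 although the two bands are equally large among respondents. Sample sensitivity, specificity, AUC and total-score correlation therefore do not describe the PD patients on whom the tool would be used. What is at stake is objective 1: the referral threshold and the accuracy reported with it.

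**Working it through.** **The plan's own figure.** Netherlands 10 low + 20 high; Austria 20 low + 50 high. High: 20 + 50 = 70. Low: 10 + 20 = 30. Total 100, as stated. Middle band: 0. The article states no precision calculation to reproduce.

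**What needs no model.** Moving a cut-off from the 30th to the 70th percentile reclassifies none of the 100 patients on the selection score. Sample sensitivity and specificity are constant across the gap.

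**Model for the size (assumed).** Standard normal total score x; a disorder D is present when a normal variable with correlation ρ to x exceeds t = Φ⁻¹(1 − prevalence). Then P(D|x) = Φ((ρx − t)/√(1 − ρ²)). The documents give neither input, so ρ = 0.3-0.6 and prevalence 30-70% are used. Selection is taken to be on the total score.

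**Where the true optimum lies.** Sensitivity + specificity is greatest where P(D|x) equals the prevalence, so x* = t(1 − √(1 − ρ²))/ρ. For ρ = 0.6 and prevalence 30%: t = 0.524 and x* = 0.524 × 0.2/0.6 = 0.175, the 57th percentile. At 70% it is −0.175, the 43rd. Smaller ρ moves it closer to the median. A search over a simulated population agrees to within a point or so (about the 44th to 58th in one run). All values lie inside the unsampled band.

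**Accuracy at a cut-off in the gap.** Let h and l be the disorder proportions in the top and bottom 30%.

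- Sample sensitivity = 70h/(70h + 30l)
- Sample specificity = 30(1 − l)/(30(1 − l) + 70(1 − h))

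At ρ = 0.5 and prevalence 50%, h = 0.739 and l = 0.261. Sensitivity = 51.7/(51.7 + 7.8) = 0.87. Specificity = 22.2/(22.2 + 18.3) = 0.55. The true values across the gap run from 0.84/0.44 (30th percentile) through 0.67/0.67 (median) to 0.44/0.84 (70th).

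Population → planned sample, at the median cut-off:

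| ρ, prevalence | Sensitivity | Specificity | AUC |
|---|---|---|---|
| 0.3, 30% | 0.640 → 0.845 | 0.560 → 0.379 | 0.641 → 0.653 |
| 0.3, 70% | 0.560 → 0.769 | 0.640 → 0.500 | 0.641 → 0.670 |
| 0.5, 50% | 0.667 → 0.868 | 0.667 → 0.548 | 0.730 → 0.765 |
| 0.6, 30% | 0.791 → 0.947 | 0.625 → 0.483 | 0.787 → 0.794 |
| 0.6, 70% | 0.625 → 0.836 | 0.791 → 0.765 | 0.787 → 0.852 |

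Over the whole grid, sensitivity is raised by 0.16-0.21, specificity lowered by 0.03-0.18, and AUC raised by 0.01-0.07.

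**Where 100 patients would put the cut-off.** In repeated simulated samples, the planned design put the empirical optimum in one of the two sampled tails about 84-97% of the time. An unselected sample of 100 put it between the 30th and 70th percentile about 71-92% of the time.

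**Total-score correlation.** Each tail has mean ±1.159 and second moment 1.608. The sample mean is (0.7 − 0.3) × 1.159 = 0.464 and the variance 1.608 − 0.215 = 1.393. Hence r(sample) = 1.180r/√(1 + 0.393r²): 0.30 becomes 0.35, 0.44 becomes 0.50, 0.60 becomes 0.66.

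**Can weighting repair it?** Weighting the two bands equally at ρ = 0.5, prevalence 50%, gives sensitivity h/(h + l) = 0.739/1.000 = 0.74, specificity also 0.74, and AUC 0.79. The population values are 0.67, 0.67 and 0.73. In this model 35-42% of patients with a disorder score in the middle band, and no weight can represent them. With middle scorers included and weighted (40/30/30 or 30/40/30 high/middle/low), 100 patients recover 0.67, 0.67 and 0.73.

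**The case against.** Extreme-group sampling has a purpose. Examination capacity is limited, and contrast helps the association analyses planned in the same patients. That stands for those analyses, but contrast does not help to choose a threshold.

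Several stronger readings are tempting and go beyond the documents:

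- **All cut-offs fail.** Selection appears to be on the overall score, so intermediate domain scores can still be observed. The gap bears on the total score; the four domain cut-offs are less affected.
- **The ICC hypothesis is met artificially.** The 0.5 threshold is stated for domain scores. The rise from 0.44 to 0.50 concerns the total-score correlation, for which no threshold is given, and the formula is for a Pearson correlation.
- **All accuracy measures are inflated.** Unweighted specificity at a median cut-off goes down. The AUC bias at ρ = 0.5, prevalence 50%, is about 0.035, below one standard error at this sample size (about 0.05).
- **Nobody in the middle, whatever is analysed.** If the questionnaire repeated in phase 2 were used, about 21-28% of patients would fall in the middle band (assumed retest correlation 0.9-0.8). They would still all come from the extremes, and the article does not state this use.
- **No correction for choosing and assessing a cut-off in the same patients.** An article may leave such detail to the full analysis plan, so its absence here is no fault.

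Setting the bands once 250 questionnaires are in may shift their limits slightly, but it does not fill the gap. It is also fair that reallocating places may no longer be possible.

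**Conclusion.** The point holds for the total score. The selection rule and the planned cut-off analysis are both explicit in the article and do not fit together, and no later analysis choice can supply the missing middle scorers. That the cut-off cannot be distinguished within the gap follows from the design alone, provided the phase 1 selection score is the one analysed. That the optimum lies in the gap, and the sizes of the distortions, rest on the normal model with assumed correlation 0.3-0.6 and prevalence 30-70%. The directions were the same throughout that range. The serious effects are the unsupported referral threshold and the overstated sensitivity (0.16-0.21 at a median cut-off). The AUC effect is modest.

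**What to change.** **If phase 2 places remain.** Keep n = 100 and give the open places to respondents between the 30th and 70th percentile. Weight the total-score ROC, sensitivity, specificity and correlation by the inverse sampling fraction of each band. With 40/30/30 high/middle/low, for example, the relative weights would be 0.30/0.40 = 0.75, 0.40/0.30 = 1.33 and 0.30/0.30 = 1. State which administration of the VIPD-Q is analysed. The cost is a short amendment, somewhat wider intervals from weighting, and less contrast for the association analyses. No extra patients are needed.

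**If recruitment is complete.** Withdraw the claim of an optimal total-score cut-off and of population sensitivity, specificity and AUC. Report the proportion with each disorder in the high and low score bands, and state that middle scorers were not examined. This costs only a change of wording and a narrower conclusion for objective 1.
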